### 3.3.3 Setting

Cost and facility performance data will be collected from all 36 sites. See Section 3.1.3 for a list of the site selection criteria.

### 3.3.4 Population

For the purpose of the sample size calculation, the unit of analysis is the site. Calculations of the number of sites required and statistical power focused on two malaria indicators and site-level data from eight Joint Uganda Malaria Training Program sites 120 days before training and 120 days after training. The mean change and standard deviation among the eight sites are in columns 1 and 2 of Table 4. The proposed evaluation is designed to detect an 18- point (20-point) difference between the treatment and the control group. Calculations of the number of sites required were based on a power of 80% and alpha of .05 using the sample size program in Stata version 10. Table 3 shows four calculations using two indicators for two different age groups. Column 3 indicates that 18 sites are required per treatment group to achieve 80% power for the first indicator for patients 5 years or more, but that the proposed design of 16 per group will be adequate for the others. Similarly, column 4 indicates that the proposed design will have only a 76% chance of detecting a difference of 10 points for the first indicator for patients 5 years or more, but that that there is a high probability (81% to 100%) of detecting differences for the other indicators. It is likely that the proposed design will provide sufficient power for other indicators as well. If site-level covariates are added to the site-level regression analysis, the power may be higher than shown here.

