**Box 1. Uganda’s Public Health Facilities**

11 Regional Referral Hospitals – 2,000,000 served per hospital

55-70 District Reference Hospitals – 500,000 served per hospital

150-200 Health Center IV (primarily clinical officers and nurses) – 100,000 served per center

900-1000 Health Center III (primarily clinical officers and nurses; no lab services) – 20,000 served per center

**The population in the areas surrounding the proposed sites will benefit directly from lower infection, illness and mortality rates.** The improved ability of clinic staff to deliver quality prevention and care services will increase access to cost-effective interventions delivered according to national guidelines by 9% to 25% depending on the intervention.

**IDCAP will provide definitive evidence on the cost-effectiveness of on-site support.** The results on the cost-effectiveness of on-site support services including Continuous Quality Improvement (CQI) activities and on-site training for multidisciplinary teams) could potentially encourage investment away from up-front classroom-based training programs, and toward the workplace capacity building programs widely suspected to have more long-lasting results.

**Results of this evaluation will enable more efficient use of donor investment.** This evaluation seeks to identify the nature of the ideal capacity-building program for MLP in Uganda, enabling the considerable amount of global resources to focus on its replication throughout Africa and the developing world. Large donors will be encouraged to support the whole or a portion of an integrated infectious disease training program rather than disease-specific training approaches currently being employed. Demonstration of achieved competence in treating and preventing multiple infectious diseases will hopefully dissuade donors from continuing the currently inefficient and redundant efforts found in disease-specific training programs.

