### Based on IDI’s experience with the Joint Uganda Malaria Training Program (JUMP), the Core IDT was designed for two participants from each site. As explained in Section 3.3.4 with the sample size calculations for the facility cost and performance indicators, a sample size of 18 sites per treatment group or total of 36 sites was required. Consequently 72 participants would attend the Core IDT course. The evaluation is adequately powered to assess changes in case scenario scores, particularly as we have observed changes of double the magnitude that were used in the sample size calculations.

###

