**Table 4: Sample size calculations to test the effect of on-site support on malaria indicators**

| **Indicator** | **Mean difference** | **Standard Devia-tion** | **Numbe of sites required for power of 80%** | **Power of estimates when number of sites is 16** |
| --- | --- | --- | --- | --- |
| **% of patients with a lab test for malaria among people suspected to have malaria** |  |  |  |  |
| Children < 5 years | 18 | 18 | 16 | 76% |
| Patients 5 or more years | 18 | 19 | 18 | 81% |
| **% with a negative laboratory test for malaria who are treated for malaria** |  |  |  |  |
| Children < five years | 20 | 12 | 6 | 100% |
| Patients 5 or more years | 20 | 10 | 4 | 100% |

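### Section 3.3.4 misstates the power of the main facility comparison: 76% is attached to a 10-point difference, two powers in Table 4 are swapped, and 16 sites per group are used where the trial has 18

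*Protocol*

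**What the plan says.** Section 3.3.4 sizes the randomised comparison of sites on two malaria indicators, each in two age groups. The target is stated first: "The proposed evaluation is designed to detect an 18- point (20-point) difference between the treatment and the control group". The site numbers were "based on a power of 80% and alpha of .05", with SDs of change from eight earlier training sites.

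The text then reads off Table 4. For the first indicator (laboratory testing of malaria suspects) it says that 18 sites per group are needed in patients aged 5 or more, but that "the proposed design of 16 per group will be adequate for the others". On power, it says that for those same patients the design "will have only a 76% chance of detecting a difference of 10 points for the first indicator", and it gives 81% to 100% for the other rows.

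Table 4 prints, for the first indicator, a difference of 18 in both age groups. Children under 5 have SD 18, 16 sites required and 76% power. The older group reads "Patients 5 or more years | 18 | 19 | 18 | 81" (per cent). The power column is headed as applying to 16 sites.

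Elsewhere the design is 18 sites per group. Sections 2.3, 2.5 and 3.3.1 say so, and Section 3.2.4 cites Section 3.3.4 as its source: "a sample size of 18 sites per treatment group or total of 36 sites was required".

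**The concern.** Three statements about the same calculation disagree. The text attaches 76% to 10 points, while the paragraph's own target and the table row it describes are 18 points. The text gives the 76% to older patients and the table gives it to young children. The text and the power column describe 16 sites per group, while the protocol randomises 18.

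This is the only power statement for hypothesis 2, the main randomised comparison. Someone who takes it at face value would believe the trial had about three chances in four of detecting a 10-point effect on malaria testing in older patients. A null result on that indicator would then be read as stronger evidence against a 10-point effect than it is. Nor does the section state any power for the design actually being run.

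**Working it through.** **Inputs.** From Table 4: differences of 18, 18, 20 and 20 points, with SDs of 18, 19, 12 and 10. From Section 3.3.4: alpha 0.05, target power 80%. Sites per group: 16 (Section 3.3.4 and Table 4) or 18 (Sections 2.3, 2.5, 3.2.4 and 3.3.1). Sidedness is not stated; two-sided is assumed because it reproduces the table, whereas one-sided would give 13, 14, 5 and 4 sites.

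**Step 1: reproduce the sites-required column.** n per group = 2 × [(1.960 + 0.842) × SD / d]².

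| Row | d / SD | n | Table 4 |
|---|---|---|---|
| First indicator, under 5 | 18 / 18 | 15.7 → 16 | 16 |
| First indicator, 5 or more | 18 / 19 | 17.5 → 18 | 18 |
| Second indicator, under 5 | 20 / 12 | 5.7 → 6 | 6 |
| Second indicator, 5 or more | 20 / 10 | 3.9 → 4 | 4 |

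All four match, so the method and inputs are the protocol's own.

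**Step 2: power at 16 sites per group.** Power = Φ(d/SD × √(n/2) − 1.96), with √(16/2) = 2.828.

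- 18 points, SD 18: Φ(2.828 − 1.96) = Φ(0.868) = 80.7%. Table 4 prints 76%.
- 18 points, SD 19: Φ(2.680 − 1.96) = Φ(0.720) = 76.4%. Table 4 prints 81%.
- 20 points, SD 12: 99.7%. 20 points, SD 10: 99.99%. Table 4 prints 100% for both.

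The first two printed powers are therefore swapped. This shows without calculation: a row that needs 18 sites for 80% power cannot have 81% with 16, and a row that needs 16 cannot have 76% with 16.

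**Step 3: the 10-point statement.** First indicator, patients 5 or more, SD 19.

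- 16 per group: Φ(10/19 × 2.828 − 1.96) = Φ(−0.471) = 31.9% (t-test 30.2%).
- 18 per group: Φ(10/19 × 3 − 1.96) = Φ(−0.381) = 35.2% (t-test 33.6%).
- One-sided alpha, the most favourable variant tried: 43.8% and 47.4%.

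None approaches 76%. That figure is reproduced by 18 points, SD 19 and 16 sites (Step 2).

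**Step 4: power at 18 sites per group**, with √(18/2) = 3.

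| Row | At the design difference: normal | At the design difference: t-test | At 10 points: normal |
|---|---|---|---|
| First indicator, SD 18 | 18 points: 85.1% | 83.0% | 38.5% |
| First indicator, SD 19 | 18 points: 81.1% | 78.9% | 35.2% |
| Second indicator, SD 12 | 20 points: 99.9% | 99.8% | Φ(2.5 − 1.96) = 70.5% |
| Second indicator, SD 10 | 20 points: >99.9% | >99.9% | Φ(3 − 1.96) = 85.1% |

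**The case against.** The strongest reply is that the 10 is an isolated slip for 18. The same paragraph states the 18-point target, the sentence reports a table row whose difference is 18, and substituting 18 returns 76% exactly. That is very probably what happened, and it limits the seriousness of the error. It does not remove it: the sentence is wrong as printed, and because the table contradicts the text on which age group has 76%, a reader cannot settle the matter by looking across.

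A second reply is that the primary analysis in Section 3.3.2 adjusts for the baseline value, and that Section 3.3.4 notes covariates may raise power. The figures above are indeed planning approximations for an unadjusted comparison. But for 76% at 10 points with 18 per group the residual SD would have to be 10 × 3 / (1.96 + 0.706) = 11.2, a variance about 65% below that implied by SD 19. The protocol offers nothing to support that.

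A third reply is that the 16-site column errs on the cautious side and that the sites-required column supports 18 per group. Both are true. The stale column understates power at the design difference.

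Some stronger readings are tempting and do not hold. A reader might infer that the trial cannot detect 10-point gains at all; but 35–38% applies to the first indicator only, and the second has about 71–85% at 10 points. A reader might also set the low end of the gains in Section 2.2, "according to national guidelines by 9% to 25% depending on the intervention", against the 18-point target. That passage concerns access to interventions, does not say whether the percentages are relative or in points, and is not tied to either indicator. Finally, taking the before/after change at eight sites as the difference between groups is a disclosed planning assumption, not an arithmetic error.

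**Conclusion.** The power statement is wrong as written in three respects. At 10 points, for the first indicator in patients 5 or more, power is about 32% (16 per group) or 35% (18 per group), less than half the stated 76%. The first two powers in Table 4 are interchanged. The calculation is presented for 16 sites per group, although 18 are randomised.

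A reader might infer that the trial is too small. The figures do not support this: at the protocol's own 18-point target with 18 per group, power is 85% and 81%, or 83% and 79% by t-test, so the hardest row falls about one point short of 80% at worst. The sentence suggesting that power is likely to suffice for other indicators can be neither confirmed nor refuted, since the section gives no SDs or differences for them.

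These results rest on a two-sided alpha of 0.05, an unadjusted comparison of site means, equal groups, and Table 4's SDs taken as known.

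**What to change.** In Section 3.3.4, change 10 points to 18 points and replace 16 per group with 18. In Table 4, relabel and recompute the power column for 18 sites per group: 85% (SD 18) and 81% (SD 19) at 18 points, or 83% and 79% if the t-test is used, and over 99% for both rows of the second indicator at 20 points. Recomputing also removes the swap. Bring the sentences that quote the column into line, and correct the reference to Table 3, which should be to Table 4.

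If power at 10 points is added, give it by indicator: about 35–38% for the first (SD 18–19) and about 71–85% for the second (SD 10–12). Qualify the sentence on other indicators by saying that their power depends on SDs and differences not given here.

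The cost is a text and table correction. The number of sites, the randomisation and the analysis do not change.

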**Table 4: Sample size calculations to test the effect of on-site support on malaria indicators**

| **Indicator** | **Mean difference** | **Standard Devia-tion** | **Numbe of sites required for power of 80%** | **Power of estimates when number of sites is 16** |
| --- | --- | --- | --- | --- |
| **% of patients with a lab test for malaria among people suspected to have malaria** |  |  |  |  |
| Children < 5 years | 18 | 18 | 16 | 76% |
| Patients 5 or more years | 18 | 19 | 18 | 81% |
| **% with a negative laboratory test for malaria who are treated for malaria** |  |  |  |  |
| Children < five years | 20 | 12 | 6 | 100% |
| Patients 5 or more years | 20 | 10 | 4 | 100% |

### A sample size calculation was not performed for the cost of the intervention, because IDCAP is the only entity providing it; i.e. the information is deterministic.3.3.5 Ethical Considerations

**Consent**

a) Sites. The district health officers where each of the sites is located and facility in-charge have been informed about IDCAP during meetings in June and August 2009. At the meetings, the roles and responsibilities of the district, health facility and IDCAP staff in building capacity and collecting data were explained. In addition, the randomization process was explained, including the role of the Phase 2 sites. Potential sites were asked to participate only if they would accept to be Phase 2 sites if they were randomly assigned to that phase.

b) Facility staff. Facility staff who participate in the OSS will also apply to the IDI. Most of the facility staff who do not attend the core IDT will be assessed on the basis of the facility performance indicators for the site. Their consent will not be required to use the facility cost and performance indicators. An exception is the laboratory staff who will be assessed on their performance during the OSS laboratory breakout sessions to see if they have met IDI standards for laboratory training. The laboratory professionals will be asked to give consent for secondary analysis of training program data. When they apply to the IDI training program, the application form will have two parts: a) course application, and b) consent to share the trainees’ data with the IDCAP evaluation. For the consent form, permission is requested to use trainee data to create a confidential record that will be used for the IDCAP evaluation. As stated on the form, “The decision is voluntary. You should feel completely free to choose not to share the data and to withdraw your data from the analysis without giving a reason.”

The OSS will include classroom sessions and clinical mentoring for all the facility staff. Observation of the staff by the mobile teams is one way that the mobile team members identify topics on which to mentor the staff. Staff will also be encouraged to identify areas in which they would like mentoring using innovative methods such as diaries. The observation is confidential; mobile team members are not supervisors and do not report performance issues to the facility in-charge or district health teams. Feedback will be given in confidence and never in the presence of patients or colleagues. It is possible that the mobile team members will witness gross incompetence on the part of one of the staff. Under circumstances when patient safety is at stake, the mobile team members will report to the facility in-charge or district health team.

Individual data will be collected on the employee engagement questionnaire. To link the responses over time, data will be collected confidentially. Employees will be exposed to minimal risk that might arise from the loss of confidentiality of the data. Each employee will be asked to give verbal consent. As explained on the consent form, completing the questionnaire is voluntary and confidential.

To maintain confidentiality, staff will be assigned a code number that will be used only for the employee engagement questionnaire. The data technicians who administer the questionnaires during the site visit will keep a key linking each staff member to his/her code number. The data technician will write the code number on the questionnaire when they give it to the staff member. The key will be kept in a locked container that the data technicians bring with them to the site whenever the questionnaires are not being administered, and a locked file cabinet at the IDCAP office.

c) Patients. IDCAP poses minimal risk to patients, because facility staff will be encouraged to comply with Ministry of Health guidelines. At this time, we would like to request a waiver from obtaining informed consent from the patients, which is recommended for quality improvement programs that have a rigorous evaluation design.[[34]](#endnote-35) IDCAP will protect the confidentiality of these data.

The exception is patients with HIV. The indicators on mortality for HIV patients will be measured from a cohort of patients who come for a visit during the first three months after the OSS begins. They will be exposed to the minimal risk of loss of confidentiality and asked to give verbal consent for IDCAP to follow their health status for 24 months. Contact information that is reported on HIV/ART cards will be collected. These patients will be asked to check with the evaluation clerk at the site each month when they come for a monitoring visit during treatment and report whether they are working and/or performing normal activities. At the end of phase 1 and 2, they will be offered a transportation refund for travel to the clinic for a total of two payments even if they complete or stop treatment. If the patient misses a monthly visit, the evaluation assistant will use the contact information to find out whether the patient has transferred out, stopped treatment, become bed-ridden or died.

**Data Storage**

Please note that the IDCAP employees sign a confidentiality agreement as a condition of their employment at IDI.

The OSS assessment of laboratory professionals will be reported in the IDI training data base as part of IDI’s monitoring and evaluation practices. Each trainee will be assigned a trainee ID number and s/he will be identified by it in the IDI training data base. The records of trainees who agree to share a confidential record will be assigned a second IDCAP number. The record will not contain the trainee’s name or demographic information that would identify him/her. The record will have an IDCAP number, and a confidential key will link the IDCAP number to the IDI training records. The confidential key will be stored securely and only the people listed on the consent form will have access to it.

The patient visit forms will be stored according to HMIS procedures at the health facility. Records for visits that did not involve follow-up will be assigned a visit ID number in the sequence in which they arrive and not have any identifying information about the patient in the data base. Records for visits that involve follow-up (e.g. someone newly diagnosed with tuberculosis) will be assigned an evaluation ID number and the patient will be identified only by that ID number in the data base. The key that links the patient to the ID number will also be kept in a locked file cabinet at the IDCAP office.

Note that the identifying information of patients with visits that involve follow-up will be transferred to data extraction form that will be used to check registers and HIV/ART cards to see if the follow-up activities occurred.

The registers and HIV/ART Cards will be stored at the health facility according to their standard operating procedures. Data including identifying information about patients will be extracted onto paper forms that will be stored and transported to IDCAP office in locked vehicles. Data will be entered and stored in password protected files of a computer at the IDCAP office. These files will be stored on an external hard drive, rather than a server. Patients will be assigned an evaluation ID numbers (not their patient ID numbers) and they will be identified only by that ID number in the data base. The key that links the patient to the ID number will also be kept in a locked file cabinet at the IDCAP office.

For the cohort of HIV patients, all contact information will be maintained in a locked box at the site by the site evaluation clerk. At the end of the evaluation, the information will be transferred to the IDCAP office. No information identifying the participant or his/her family will ever be released to anyone except for the evaluation clerk and the people listed on the consent form. Information about their health status will be recorded in the data base ID number and will exclude contact and demographic information that could be used to identify him/her. A key linking the ID number to contact information will be securely stored by the IDCAP team for five years and then destroyed.

### 3.3.6 Limitations

The success of the proposed intervention will depend on our ability to avoid duplication of the considerable efforts to date. HCI is well positioned to facilitate this effort for OSS, as it has effectively been run through the MOH since its inception. The prevalence of so many other interventions brings another challenge, which is to filter the noise and accurately assess the *incremental* impact of the proposed capacity-building program. Wherever possible, we will control for the effect of complimentary programs in our sites, but accept as a potential limitation (but ultimately, a mutual benefit for all) the fact that progress will be made on several fronts simultaneously toward higher quality healthcare.

The duration of the evaluation is three years. IDCAP focuses on capacity-building rather than supplying commodities. It is anticipated that patients will receive medications for key infectious diseases such as malaria, tuberculosis, and HIV, including anti-retroviral therapy (ART), through the MOH. People will be initiated on ART with doses allocated by the MOH rather than with IDCAP resources. Consequently, it is not anticipated that drug stock-outs at IDCAP sites after the evaluation will be worse than during the evaluation or than other health facilities in Uganda.

It is possible that IDCAP sites will experience fewer drug stock-outs after the evaluation than before. The continuous quality improvement activities of IDCAP seek to improve the processes of care and may result in improved drug procurement processes such as more accurate estimates the amount of drugs needed and more timely orders. To the extent that these improved processes are institutionalized, the supply of drugs would be better at IDCAP sites.

Please note that data on other indicators such as drug supply will continue at half of the Phase 1 sites for at least nine months after the IDT and on-site support stop, so it will be possible to measure the extent to which the improved processes are institutionalized.

